### Study Population

The study will recruit hospital in-patients and out-patients with moderate to severe depression who have been prescribed ECT by their treating psychiatrist and have been determined fit for ECT and ketamine administration by an anaesthetist. All participants will provide written informed consent. The original aim was to recruit 160 patients, however due to slow recruitment a revised target of 100 patients, and refinement of the primary outcome measure, together with a study extension, was agreed between the study team, Data Monitoring and Ethics Committee (DMEC) and Trial Steering Committee (TSC), Research Ethics Committee, the Medicines and Healthcare products Regulatory Authority (MHRA), the funder and the sponsor. The recruitment target for a sub-population drawn from those taking part in the main RCT to undergo mechanistic studies was originally 100 (revised to 20 due to slow recruitment) together with 50 matched healthy volunteers recruited for neuropsychological and fNIRS baseline testing comparisons.

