#### Patient Exclusion criteria

DSM-IV diagnosis of a primary psychotic or schizoaffective disorder, current primary obsessive compulsive disorder or anorexia nervosa.History of drug or alcohol dependence (DSM-IV criteria) within the last year.ECT in last 3 months or has previously received ECT in the current trial.Known hypersensitivity or contraindication to ketamine or excipients in the injection, including significant cardiovascular disease, uncontrolled hypertension, glaucoma, cirrhosis or abnormal liver function or liver disease.Known hypersensitivity or contraindication to concomitant medications used for ECT including propofol or suxamethonium or excipients in the injections.Evidence of organic brain disease including dementia, neurological illness or injury, or medical illness which may significantly affect neuropsychological function.Detained under the Mental Health Act (1983 as amended 2007).Pregnancy, or at risk of pregnancy and not taking adequate contraception, breastfeeding.Score of less than 24 on the MMSE [45].

Psychotropic medication-free healthy volunteers without a personal or family history of major psychiatric illness or significant medical illness will also be recruited. They will be aged over 18 years or over and will be matched as a group with patients for age and sex.

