#### Revised Power calculations

Following initial slow recruitment, the revised recruitment target was adjusted to 100 patients with 95 reaching the primary outcome measure point and the primary outcome was changed to the HVLT-R alone. This sample size provides 80 % power to detect an ES of 0.57 (ITT) and 0.58 (completer), two-sided *p* = 0.05. The target for recruitment to the mechanistic studies was decreased to a sample size of 20 patients (10 per treatment arm) and 50 controls. This has only a 21 % power to detect an ES of 0.6 with a two-sided *p* = 0.05 between the two treatment arms (10 per arm). Comparing 20 patients and 50 controls will give an ability to detect an ES of 0.6 between groups with 60 % power and two-sided *p* = 0.05, and a 70 % power to detect the same size of effect of ECT itself with a two-side *p* = 0.05.

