### Statistical Analysis

#### Neuropsychological and clinical outcomes

There are no interim analyses planned unless requested for safety reasons by the DMEC. All estimates of efficacy will be based on a modified intention to treat (ITT) analysis including patients who have received at least one ECT treatment (given that this is a study of the effect of ketamine on ECT). The main statistical inference for both neuropsychological and efficacy outcomes will be made after 4 ECT sessions. In addition, the two treatment groups will be compared at the end of acute ECT treatment and 1 and 4 months later. Analysis methods are specified in a detailed Statistical Analysis Plan approved by the DMEC and TSC (available on request). Briefly, for neuropsychological data cross-sectional analysis of covariance (ANCOVA) models (allowing for stratifying variables, age, sex, baseline degree of treatment resistance, electrode placement [bilateral or unilateral] and baseline values of the outcome being studied) will be used to evaluate the effects of treatment allocation. The sensitivity of the findings to missing data will be assessed with inverse probability weighting adjustments. All analyses will involve the use of robust standard errors and associated confidence intervals (allowing for non-normality and constraints in the ranges of some of the cognitive outcomes). Efficacy data will be analysed using a random effects (random intercepts) ANCOVA model with time (in weeks) as a quantitative explanatory variable. The baseline variables will be the same as those for neuropsychological data. An interaction term between time and treatment allocation will also be included to assess the treatment effect.

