#### Mechanistic outcomes

fNIRS data will be preprocessed with HOMER2 (http://www.nmr.mgh.harvard.edu/PMI/resources/homer2/home.htm) converting them into HbO and HbR concentration changes after noise and motion artefact correction [55]. Primary analysis will be the region of interest (ROI) covering the key frontal cortical area and consist of the anterior optical channels. Channels will be discarded for very low optical intensity or high motion artefact according to standard protocols. Stimulus blocks will be averaged and the maximum haemodynamic changes determined for both HbO and HbR concentration in a time window based on the expected peak latency of the haemodynamic response. Repeated measures analysis of variance will be performed to compare patients and healthy controls and the effect of ECT and treatment allocation in patients, assigning 0 values to the missing channels within the ROI.

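### The non-randomised fNIRS patient-control comparison is group-matched on age and sex but names no covariates; adjusting for both would be a nearly free improvement

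*Protocol article*

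**What the plan says.** Under Mechanistic outcomes, the protocol article gives the method for this contrast as "Repeated measures analysis of variance will be performed to compare patients and healthy controls". The same sentence covers the effects of ECT and of treatment allocation within patients. No covariate is mentioned for any of these.

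The healthy volunteers are described at the end of the Patient Exclusion criteria section, which says that they "will be matched as a group with patients for age and sex". The section does not say how close the match must be, or which patients it refers to.

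Study Population says that the mechanistic patient target "was originally 100 (revised to 20 due to slow recruitment) together with 50 matched healthy volunteers". It assigns those volunteers to both the neuropsychological and the fNIRS baseline comparisons. Revised Power calculations confirms that the target was "decreased to a sample size of 20 patients (10 per treatment arm) and 50 controls", and adds: "Comparing 20 patients and 50 controls will give an ability to detect an ES of 0.6 between groups with 60 % power".

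For the other outcomes, the section Neuropsychological and clinical outcomes names ANCOVA models "allowing for stratifying variables, age, sex, baseline degree of treatment resistance", along with electrode placement and the baseline value of the outcome. The efficacy model uses the same baseline variables.

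**The concern.** Randomisation protects the ketamine-saline contrast but not the patient-control contrast. The only stated protection there against confounding by age and sex is group matching, which brings the two distributions together approximately and guarantees nothing for the particular patients scanned.

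Those patients may be a selected subset. The Discussion says that distance, transport of the equipment and reluctance to undergo extra testing all limited recruitment to the mechanistic work. Volunteers matched to a wider patient group need not match the 20 who are scanned.

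Two things are at stake. First, any gap left after matching goes into an unadjusted estimate. Second, even with perfect group balance, variation in response due to age and sex stays in the error term. This matters more for a comparison with 60 % stated power than for a well-powered one. The article lists age and sex for its treatment-arm models, so their absence from the model for a non-randomised contrast stands out.

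**Working it through.** **Inputs from the article.** 20 patients and 50 controls, effect size 0.6, two-sided alpha 0.05, stated power 60 % (Revised Power calculations). The earlier patient target was 100 (Study Population).

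**Inputs that are assumptions.** The article gives none of these, so ranges are shown: d, the standardised imbalance left in a covariate such as age; r, its correlation with the haemodynamic response; R², the share of response variance explained by age and sex together.

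**1. The stated power.** For an unadjusted two-sample comparison, the standard error of the group difference in SD units is √(1/20 + 1/50) = √0.07 = 0.265. The noncentrality is 0.6/0.265 = 2.27 on 68 degrees of freedom. The noncentral t gives 60.9 %, so the stated 60 % reproduces as an unadjusted figure. (The normal approximation gives 62.1 %.)

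**2. How large a chance imbalance could be.** With no matching at all, the SD of a standardised covariate difference is √(1/n₁ + 1/n₂):

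- 100 v 50: √0.03 = 0.173; P(|d| > 0.25) = 15 %; P(|d| > 0.5) = 0.4 %.
- 20 v 50: 0.265; P(|d| > 0.25) = 34 %; P(|d| > 0.5) = 6 %.

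These are upper references only. Group matching should make both smaller.

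**3. What an imbalance would do if unadjusted.** For one covariate, bias in outcome SDs = r × d. The last two columns give the actual type I error of a nominal 5 % test.

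| d | r | Bias (SD) | Share of 0.6 | 20 v 50 | 100 v 50 |
|---|---|---|---|---|---|
| 0.1 | 0.2 | 0.02 | 3 % | 5.1 % | 5.2 % |
| 0.25 | 0.3 | 0.075 | 12.5 % | 5.9 % | 7.1 % |
| 0.5 | 0.5 | 0.25 | 42 % | 15.4 % | 30.0 % |

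The last row is an extreme case. The smaller sample makes a given d more likely, but a given d distorts the test less because the standard error is larger.

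**4. What adjustment costs and gains.** With two covariates there are 70 − 4 = 66 degrees of freedom. The noncentrality is 0.6/√[(1 − R²) × 0.07/(1 − g)]. Here g is the squared correlation between group and covariate: g = pd²/(1 + pd²), with p = 20 × 50/70² = 0.204.

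| R² | Power, d = 0 | Power, d = 0.25 |
|---|---|---|
| 0 | 60.8 % | 60.3 % |
| 0.10 | 65.4 % | 64.8 % |
| 0.20 | 70.5 % | 69.9 % |
| 0.30 | 76.1 % | 75.6 % |

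If the covariates explain nothing, the loss against 60.9 % is 0.1 point at d = 0 and 0.6 point at d = 0.25. At d = 0.5 and R² = 0, power is 58.7 %, a loss of about 2 points.

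**The case against.** The strongest reply is that this is silence in a condensed article, not a decision. The article refers to a detailed statistical analysis plan, which is not shown and may list fNIRS covariates. This stands in part: a reader might infer that adjustment has been ruled out, and the article does not say so. The correct statement is that no covariates are named. The reference to the separate plan sits under the neuropsychological and clinical heading, however, so it is unclear whether it covers fNIRS. The article also does more than stay silent: it names a specific method for this contrast.

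Second, matching already targets age and sex, and 50 controls for 20 patients can make a close match easier. This also stands as far as it goes. A reader might infer that a material imbalance exists, or that the estimate is biased by something like 17-33 % of the target effect (d = 0.5 with r of 0.2-0.4). The article supports neither. An age gap above 0.5 SD has only about a 6 % chance even with no matching.

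Third, a reader might infer that the cut from 100 to 20 patients makes confounding worse in every respect. It does not: imbalance becomes more likely, but the same imbalance inflates type I error less.

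Fourth, the models that include age and sex compare treatment arms among patients who were not matched on them, so the difference between the two sections is not a contradiction. That is right; the comparison shows only that the authors regard these variables as worth modelling.

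None of this removes the precision argument. Group matching does not take age and sex variance out of the error term.

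**Conclusion.** The point holds as a low-cost improvement, not as a demonstrated error. The method named for a non-randomised, group-matched comparison lists no covariates, and modelling the two matching variables would be better.

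The likely bias is small to modest: 0.02 SD (3 % of the target) at d = 0.1, r = 0.2, and 0.075 SD (12.5 %) at d = 0.25, r = 0.3. These figures rest wholly on assumed r and d. The 0.265 SD standard error describes unmatched sampling and serves only as an upper reference.

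The precision gain is the firmer part of the case, though its size depends on an assumed R²: power of about 65 % at R² = 0.10 and 70 % at R² = 0.20, against 60.9 % unadjusted.

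The consequence is confined to the mechanistic substudy, which the Discussion now presents mainly as an assessment of feasibility and usefulness. The randomised ketamine-saline comparison and the primary outcome are unaffected.

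**What to change.** Under Mechanistic outcomes, specify the patient-control comparison as a repeated measures ANCOVA, or an equivalent linear mixed model, with age and sex as between-subject covariates. Add that the age and sex distributions of the controls will be checked against the patients actually scanned. If the separate analysis plan already provides for this, a sentence in the article saying so is enough.

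The cost is one or two sentences and two degrees of freedom. No new data are needed, because age and sex must already be known for the matching. A linear age term removes only the linear part of any age confounding, so the check of the matching is still worth doing alongside the adjustment.

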Depression is associated with impaired frontal cortical metabolism and function [38, 39] and treatment with antidepressant drugs leads to their normalisation [38, 40]. In contrast ECT is associated acutely with a further decrease in frontal cortex metabolism [41], and one hypothesis is that the cognitive deficits seen with ECT may relate to these frontal effects [42]. If ketamine prevents cognitive deficits with ECT then a test of this hypothesis is whether ketamine prevents ECT-induced suppression of frontal cortical function.

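### Discarded fNIRS channels are analysed as a response of zero, so poor signal quality is read as low frontal activation

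*Protocol article*

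**What the plan says.** The rule is in the Protocol article, Statistical Analysis, Mechanistic outcomes. The region-of-interest analysis is the main fNIRS analysis: "Primary analysis will be the region of interest (ROI) covering the key frontal cortical area and consist of the anterior optical channels". Bad channels are removed first: "Channels will be discarded for very low optical intensity or high motion artefact according to standard protocols". The outcome is then formed: "Stimulus blocks will be averaged and the maximum haemodynamic changes determined for both HbO and HbR concentration". The model serves three contrasts: "Repeated measures analysis of variance will be performed to compare patients and healthy controls and the effect of ECT and treatment allocation in patients". It is run by "assigning 0 values to the missing channels within the ROI".

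The section describes no centring or standardisation that would make zero a neutral value. It states no minimum number of valid channels, no adjustment for the share lost and no sensitivity analysis for channel loss. The inverse probability weighting elsewhere in the article is described for neuropsychological and clinical outcomes. The SAP was not available for this review, but the zero rule is stated in the article itself and is not a detail left to the SAP.

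**The concern.** A channel is discarded because nothing usable was recorded. Entering zero replaces that ignorance with a definite observation, namely that the cortex under the channel did not respond. The ROI signal then depends on two things, the true response and the share of usable channels, and the ANOVA cannot separate them.

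The Background says that depression involves impaired frontal function, that ECT lowers frontal metabolism further, and that the test is "whether ketamine prevents ECT-induced suppression of frontal cortical function". Worse signal in patients than in healthy volunteers, or after ECT than before it, would produce the first two parts of that pattern with no difference in brain response. Unequal loss is plausible. The Discussion describes patients as severely ill and many as reluctant to undergo extra testing, and the equipment may be taken to patients at other sites. The controls are medication-free volunteers matched only as a group on age and sex. Nothing in the design equalises signal quality.

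At stake is the whole second secondary aim, which rests on this analysis. A reader of the results could not tell an artefact from an effect.

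**Working it through.** **Inputs from the Protocol article.** The zero rule, the reasons for discarding, the peak-change outcome and the three contrasts are in Mechanistic outcomes. The sub-study was "decreased to a sample size of 20 patients (10 per treatment arm) and 50 controls" (Revised Power calculations), with two-sided tests at 0.05. No stated figure lies behind the zero rule, so there is none to reproduce.

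**Inputs not in the documents (assumed).** Channel-loss shares, number of ROI channels, and the ratio of mean response to between-subject SD.

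**Step 1: effect on the mean.** Take K channels with mean response μ and a share f lost, with loss unrelated to the true response:

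zero-filled ROI mean = [(1 − f)K·μ + fK·0] / K = (1 − f)μ.

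The result is the same whether channels are averaged first or entered as a factor, because the marginal mean over channels shrinks by the same factor. It applies to HbO and HbR alike and is a shift towards zero. For HbO, zero may even lie below the no-activation level, since the maximum over a noisy time window tends to be positive.

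**Step 2: spurious difference with equal true responses.** Ratio = (1 − f_patients)/(1 − f_controls).

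| Loss, controls | Loss, patients | Ratio | Apparent reduction |
|---|---|---|---|
| 5% | 10% | 0.90/0.95 = 0.947 | 5.3% |
| 5% | 20% | 0.80/0.95 = 0.842 | 15.8% |
| 5% | 30% | 0.70/0.95 = 0.737 | 26.3% |
| 10% | 10% | 0.90/0.90 = 1 | 0 |
| 10% | 20% | 0.80/0.90 = 0.889 | 11.1% |
| 10% | 30% | 0.70/0.90 = 0.778 | 22.2% |

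The same arithmetic applies within patients: 10% loss before ECT and 20% after gives an apparent fall of 11.1% with no change in response.

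**Step 3: false-positive rate, 20 patients against 50 controls, no true difference.** Simulations used a two-sample t-test on the ROI mean, with loss varying between people (beta distribution).

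Setting A: 24 channels, mean 1, between-subject SD 0.6, 2,000 trials per row.

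| Loss, patients v controls | Zero-filled | Valid channels only |
|---|---|---|
| 20% v 5% | 14.7% | 5.1% |
| 30% v 10% | 26.4% | 4.1% |

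Setting B: 12 channels, channel SD 1, mean 1, beta concentration 5, 4,000 trials per cell, 10% loss in controls.

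| Loss in patients | Zero-filled, mean/SD = 1 | Zero-filled, mean/SD = 2 |
|---|---|---|
| 10% | 4.8% | 5.2% |
| 20% | 6.0% | 10.6% |
| 30% | 10.6% | 29.2% |
| 40% | 22.0% | 56.9% |

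With valid channels only, setting B gave 4.9% to 6.4% throughout, and the mean spurious difference was at most 0.01 in absolute value.

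**Step 4: equal loss.** With the same average loss m in both groups there is no spurious difference, but a true raw difference d becomes (1 − m)d. Loss that varies between people also adds variance. Take m = 0.20, beta concentration 5, mean 1, SD 0.5, and ignore channel noise:

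- Var(f) = 0.20 × 0.80/6 = 0.0267
- zero-filled variance = (0.64 + 0.0267)(1 + 0.25) − 0.64 = 0.193, SD 0.440
- standardised difference = 0.80d/0.440 = 1.82d, against d/0.5 = 2d without loss, about 9% smaller.

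This erodes a sub-study whose stated power between arms is already 21% for an effect size of 0.6.

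**The case against.** The best defence concerns reach, not the rule itself. fNIRS serves the second of two secondary aims in a sub-sample of 20 patients. The article says power for ketamine effects will be very low and presents the work partly as a feasibility exercise. No cognitive or efficacy outcome is affected. That is correct, and it limits the consequences to the sub-study.

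Second, a false difference needs unequal loss, and the document reports no loss rates. Motion correction precedes the analysis, and the controls are matched as a group on age and sex. This also stands: unequal loss is an inference, and neither step guarantees equal loss.

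Third, the ketamine contrast differs from the other two. Allocation is randomised and researchers are blinded, and nothing suggests less channel loss on ketamine. There the expected effect is attenuation, plus chance imbalance with 10 per arm. The directional worry therefore belongs to patients against controls and to before against after ECT.

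Fourth, the false-positive rates depend strongly on the assumed mean/SD ratio and come from a t-test on the ROI mean, not the planned ANOVA; only the patient-control contrast was simulated. They show a range and do not predict the trial's error rate. For HbR the shift is towards zero, so whether it counts as lower depends on the sign of the response.

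Finally, valid-channel means are unbiased only if loss is unrelated to the true response. If particular locations are lost more often in one group, they too can mislead. This favours a model with channel effects; it does not rescue zero-filling.

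**Conclusion.** The point holds. The article fixes a rule that records unmeasured channels as non-responding ones, and nothing in it neutralises the effect. The shrinkage to (1 − f) of the true mean follows from the rule, given loss unrelated to the true response.

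The size of any spurious difference is unknown, because loss rates are not given. Over assumed losses of 5–10% in controls and 20–30% in patients, the apparent reduction is 11% to 26%. The simulated false-positive rate at a nominal 5% ranges from 6% to 29%, against 4% to 6% with valid channels only. Equal loss creates no false difference but weakens a true one. The rule governs the main fNIRS analysis and hence the second secondary aim; the HVLT-R and clinical outcomes are unaffected.

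**What to change.** Delete the zero-assignment rule and treat discarded channels as missing, in one of two ways:

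- define the ROI value as the mean of valid channels, with a preset minimum number below which the ROI value is missing for that visit; or
- fit a mixed model to channel-level data with channel and participant effects, using the available channels. This is preferable if losses cluster at particular locations.

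Report the share of discarded channels by group, arm and visit, so that readers can judge whether loss was balanced. Zero-filling may be kept at most as a labelled sensitivity analysis.

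The cost is a short change to the analysis specification and script, with no new data. A few participants may lose an ROI value where too few channels are valid, which matters slightly in a sample of 20 patients and is a reason to fix the minimum before results are seen.

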### Status of the Study

The study was registered on 30/07/2012 (ISRCTN14689382) under the public title “Ketamine ECT study”. Clinical Trial Authorisation was given by the Medicines and Healthcare products Regulatory Agency (MHRA: EudraCT: 2011-005476-41). Ethical approval was granted by the North West-Liverpool East Research Ethics Committee (REC Ref No. 12/NW/0021) on 25/01/2012. Recruitment commenced in December 2012 and an extension to the study and to recruitment was granted by the funder in 2014, with the study finishing in late 2015.

